## Abstract

**Background:**

Home-based cardiac rehabilitations (CRs) with digital technologies have been researched and implemented to replace, augment, and complement traditional center-based CR in recent years with considerable success. One problem that technology-enhanced home-based CR can potentially address is the gap between cardiac interventions and formal CR programs. In the Netherlands and some other countries (eg, Australia), patients after cardiac interventions stay at home for 3-4 weeks without much support from their physicians, and often engage in very little physical activity (PA). A home-based exercise program enabled by digital technologies may help patients to better prepare for the later center-based CR programs, potentially increasing the uptake rate of those programs.

**Objective:**

In a randomized controlled trial (RCT), we will evaluate the effectiveness of a home-based walking exercise program enhanced by self-tracking and mobile-based coaching (treatment condition), comparing it with a version of the same program without these technologies (control condition). The added value of the digital technologies is justified if patients in the treatment group walk more steps on average (primary outcome) and show better physical fitness in a bicycle ergometer test and higher self-efficacy toward PA (secondary outcomes).

**Methods:**

Based on a power analysis, we will recruit 100 cardiac patients and assign them evenly to the 2 parallel groups. Eligible patients are those who are scheduled in the postanesthesia care unit, know the Dutch language, have basic literacy of using smartphones, and are without medical conditions that may increase risks associated with PA. In a face-to-face meeting with a nurse practitioner, all patients are prescribed a 3-week exercise program at home (2 walking exercises per day with increasing duration), based on national and international guidelines and tailored to their physical conditions after cardiac intervention. Their physical activities (daily steps) will be measured by the Axivity AX3 accelerometer worn at hip position. Patients in the treatment group will also be supported by a Neo Health One self-tracking device and a mobile platform called Heart Angel, through which they are monitored and coached by their nurses. After the study, all patients will perform a bicycle ergometer test and return the devices within 1 week. In addition, 5 questionnaires will be sent to the patients by emails to assess their self-efficacy toward PA and other psychological states for exploratory analyses (at discharge, at the end of each monitoring week, and 1 week after the study). To minimize bias, the randomization procedure will be performed after introducing the exercise program, so the nurse practitioners are blind to the experimental conditions until that point.

**Results:**

The study protocol has been approved by the Medical Research Ethics Committees United on February 26, 2018 (NL 62142.100.17/R17.51). By the end of 2018, we completed a small pilot study with 8 patients and the results based on interviews and app usage data suggest that a larger clinical trial with the targeted population is feasible. We expect to complete the RCT by the end of 2021, and statistical analyses will follow.

**Conclusions:**

Results of the RCT will help us to test the hypothesized benefits of self-tracking and mobile-based coaching for cardiac patients in home-based exercise programs during the discharge–rehabilitation gap. If the results are positive, cost-effectiveness analysis will be performed based on the insights of the study to inform the translation of the technology-enhanced program to clinical practice. We also note limitations of the trial in the discussion.

**Trial Registration:**

Registered at Netherlands Trial Register NL8040; https://www.trialregister.nl/trial/8040

**International Registered Report Identifier (IRRID):**

PRR1-10.2196/16737

## Introduction

Cardiac rehabilitation (CR) is an evidence-based and widely recommended strategy for the secondary prevention of cardiovascular diseases. Recent reviews have shown that CR is efficacious and cost-effective not only for reducing mortality by up to 26%, but also for preventing hospital re-admissions and improving quality of life [1-4]. In the Netherlands, after cardiac intervention, such as coronary artery bypass graft surgery, it is a standard practice to refer patients to participate in outpatient rehabilitation programs for 6-12 weeks, where group-based trainings of physical activity (PA), nutrition, and other lifestyle aspects are applied [5]. However, despite the proven benefits and the enforced practice, a general challenge for CR worldwide is the low rate of participation and completion by patients [5-8]. According to a Dutch cohort study [5], although patients after cardiac surgeries had the highest uptake rate among all cardiac patients, the number was just above 50%.

A particular challenge in the Netherlands is that there is usually a gap of 3-4 weeks between the discharge after cardiac surgery and the start of the formal CR, during which patients stay at home without much guidance on what they can do to improve their fitness. The same issue has also been reported in Australia [6]. The lack of guidance, combined with their low levels of self-efficacy for PA after surgery [9] and sometimes their preceding sedentary lifestyle, results in postsurgery PA levels that are below the level needed for optimal recovery [10]. Therefore, there is clearly a missed opportunity in this gap, which could be used to better prepare patients for the formal CR programs and even to increase the uptake rate of the programs. Moreover, because people are generally more susceptible to behavior change right after disruptive life events (eg, a cardiac surgery) [11], training patients at home for regular PA may also foster a long-term active lifestyle. To realize this opportunity, a home-based solution for supporting PA is needed.

In recent years, home-based CR has been gradually accepted as an alternative to the more traditional center-based CR. Evidence has been accumulated that home-based CR programs are often as effective as center-based CR programs [12-15], and they may incur lower costs [16,17] (but see [18]). A practical barrier for traditional CR is also eliminated as patients can stay at home and contact doctors or trainers through information and communication technologies (ICTs) only when necessary. Although long-term effects of home-based CR on PA and fitness are still in question [16], for our goal of preparing patients for the formal CR, a home-based approach is well suited in theory. However, most of the studies on applying ICTs in CR have focused on either replacing traditional CR with home-based CR [16,19] or augmenting ongoing center-based CR with new technologies [20,21], but much less on complementing the existing CR practice. One recent study examined the potential benefits of an internet- and mobile-based intervention on the maintenance of PA after regular CR, but the high attrition rate in the randomized controlled trial (RCT) prevented the authors from drawing clear conclusions [22]. More relevant to our research question, an ongoing RCT was designed to evaluate the use of SMS text messaging to support patients in the transition period after acute coronary events and before the start of CR [6]. More research is clearly needed to understand whether home-based interventions with ICTs before or after center-based CR are beneficial to patients.

Designing a cost-effective home-based PA intervention also raises the question of what intervention components are essential for an intervention to be efficacious. One component emphasized and utilized in almost all CR programs is personalized guidance from physicians based on patient monitoring [16], which can be implemented through several different communication modalities, including face-to-face meetings [23], phone calls [16], SMS text messages [24], and chat sessions using websites or mobile apps [19]. From a theoretical perspective, physician guidance plays multiple roles, such as goal setting, social persuasion, and emotional support, and it can even be more important for patients who have low cognitive capacities, or low self-efficacy toward PA after surgery [9,10]. Regardless of which modality to use, any physician guidance will increase workloads for health care professionals, so its benefits and costs are ought to be carefully weighted.

Another promising component is the self-monitoring of behavior and health status by patients themselves, usually supported by mobile and wearable self-tracking devices. Psychological theories generally consider self-monitoring as an important mechanism in self-regulation [25], and meta-analyses have demonstrated the effectiveness of self-monitoring as a behavior change technique [26]. Several RCTs examined the applications of self-tracking technologies in related clinical settings [27-29]. In one trial after myocardial infarction [27], patients who were required to record their weight, PA levels, blood pressure, and heart rate during a standard CR program reported higher self-efficacy toward PA and also exercised more than their peers in the control group 1 year later. In another trial [28], the use of pedometer alone led to higher levels of PA that were maintained 6 weeks and 6 months after a CR program. Finally, in [29], patients who wore an electronic step tracker and followed a home-based CR program showed similar levels of physical improvements to those who followed a center-based CR program.

In this study, we compare the effectiveness of 2 home-based PA programs that fill the gap between discharge and formal CR for patients after cardiac surgery, one with the support of digital technologies and one without this support. In the technology-enhanced group (intervention group), patients use a wristband to track their steps and communicate with physicians through a mobile app for 3 weeks. In the control group, patients are only told to follow a specific PA program at discharge, but do not receive any additional support while at home. Both trial conditions can be considered as clear improvements over the usual care, but they may differ greatly in their effectiveness and costs. We hypothesize that the use of self-tracking and mobile-based coaching will lead to higher PA levels and potentially also bring physical and psychological benefits at the end of the program, which would provide a rationale to implement these technologies into clinical practice. At the same time, costs associated with the technology-enhanced program can be estimated and used in cost-effectiveness analysis in the future.

## Methods

### Design

The study (registered at Netherlands Trial Register NL8040) will have a parallel-group randomized experimental design with an allocation ratio of 1:1. Participants will be randomized to the intervention or the control group during the introduction meeting at the date of discharge (Figure 1). Variables regarding participants’ psychological states (eg, self-efficacy toward PA) will be measured repeatedly over the weeks during the experiment (see the “Outcomes” section for details). The protocol conforms to the SPIRIT 2013 statement [30] and is described according to the CONSORT-EHEALTH checklist [31] (Multimedia Appendix 1).

**Figure 1 figure1:**
[figure not shown]
Design of the randomized controlled trial.

### Eligibility and Recruitment

Patients who are expected to undertake a cardiac intervention at Catharina Ziekenhuis Eindhoven (CZE) and to follow a conventional CR program at least four weeks after discharge are eligible for this study. Eligible patients should also be scheduled as postanesthesia care unit patients, who are at relatively low risk and are expected to recover smoothly. Definition of postanesthesia care unit patients is well-operationalized in preoperative workup. Other inclusion criteria are (1) the patients are in possession of an Android or an iOS device (eg, a smartphone or a tablet), and have sufficient level of digital literary to use the device (eg, regular previous uses of emails and mobile apps); and (2) they understand the Dutch language. Patients are excluded if they are immobile, have a history of stroke with remaining dysfunction, or have serious complications, including stroke, severe myocardial infarction with echocardiography-confirmed myocardial function loss, or a serious infection that requires prolonged hospital stay and intravenous antibiotics.

Patient are always screened at the outpatient clinic at least three weeks before the operation. During the screening, information concerning the study are provided and the patient is given enough time (at least one week) to read the information and to ask questions. Signing the informed consent takes place during the admission 1 or 2 days before the operation.

### Sample Size Calculation

We used a minimum effect size of interest approach to calculate the sample size needed to detect a statistically significant difference between the intervention group and the control group in terms of the primary outcome (average daily steps over 3 weeks). In an internal discussion between researchers, physicians, and CR experts at CZE, a 2000-step daily difference was proposed to be the minimum effect size of interest, and a 3000-step within-group standard deviation was assumed based on [32]. These assumptions amount to a moderate to strong effect size in terms of Cohen *d* of 0.67, which is justifiable given the large differences between the two conditions in terms of costs. Based on a simulation study in the R statistical programming environment [33], 100 participants (50 in each group) are required to have a 90% power to detect the effect at a significance level of .05. Because we will also have day-level data for steps over 3 weeks, multilevel regression models can also be used for examining the differences in PA between the two groups, which should have much higher power due to the large number of observations (ie, data collected over 21 days by 100 patients). Details of the simulation-based power analysis (and the R code) can be found in Multimedia Appendix 2.

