### Primary and Secondary Outcomes

The primary outcome is the amount of daily physical activities by the patients, operationalized as the average daily steps over the 3 weeks. The steps are measured by the Axivity AX3 tracker, which is a CE-marked 3-axis logging accelerometer developed by the Open Movement organization at Newcastle University (Figure 5). The device is intended to be used in research on activity recognition, motion measurement, medical research, and movement science. It has been used previously in a large-scale clinical trial in UK [39] and validated for measuring PA in older adults [40]. Patients in both intervention and control group will be asked to wear the device as a clip on their cloths at their hip on the nondominant side (eg, a belt clip). The device has a long battery life (around 1 month) and large internal memory (1-month’s data with a sampling frequency of 50 Hz), so the patients do not have to worry about charging the device or offloading the data. Unlike the self-tracking device (the Neo Health One), this measurement device only records data but provides no feedback about steps to the patients.

In addition to the primary outcome, 2 secondary outcomes are used to test whether the behavioral-level increase of daily PA levels would bring patients benefits at physical and psychological levels for their preparations for the formal CR program. To measure physical fitness, a bicycle ergometer test will be held for each patient at the Cardiac Function Department as their usual clinical practice within 1 week after the 3-week trial. The research team will not be involved in the administration of the test, but 3 parameters of interest, namely, peak oxygen uptake (peak VO_2_), maximal workload, and maximum heart rate (HR_max_), will be provided to us. Previous studies have shown positive effects of walking trainings on physical fitness [41-43]. However, because of the short duration and moderate intensity of our exercise program, we do not strongly predict significant effects given the sample size.

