### Statistical Analysis

For the outcome variables of interest, that is, average daily steps, overall compliance rate, and physical fitness measured in the bicycle ergometer test (peak VO_2_, maximal workload, HR_max_), the following 2-step procedure will be used. In the first step, independent sample *t* tests (unpaired) will be used to compare the outcome variables between the two study conditions. Second, when potential confounding variables are identified post hoc, they will be added to multiple regression models to control for their influences. For step data at the day level, multilevel models will be built to test the same hypotheses, with patient ID as the grouping variable [55]. We will use the conventional α level of .05 to judge for statistical significance, and more importantly to use the estimated effect sizes in order to judge the clinical significance of the effects.

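### The Sample Size Calculation wrongly credits day-level multilevel models with much higher power: for the group difference they have essentially the same power as the t test on 3-week averages

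*Protocol article*

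**What the plan says.** The primary outcome is one number per patient: daily physical activity, "operationalized as the average daily steps over the 3 weeks" (Primary and Secondary Outcomes). For the sample size, "a 2000-step daily difference was proposed to be the minimum effect size of interest" and "a 3000-step within-group standard deviation was assumed", which the Sample Size Calculation expresses as a Cohen d of 0.67. By simulation, "100 participants (50 in each group) are required to have a 90% power to detect the effect at a significance level of .05". The same section then says that multilevel regression on the daily step counts can also be used to examine the difference between the groups, "which should have much higher power due to the large number of observations (ie, data collected over 21 days by 100 patients".

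The Statistical Analysis section lists unpaired t tests first. For day-level steps it plans multilevel models grouped by patient, directed at the same hypotheses. Design and Randomization and Blinding make clear that each patient is allocated once, 1:1, at the introduction meeting.

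**The concern.** Treatment differs between patients and never within a patient. The precision of the group comparison is therefore limited by how many patients there are and how much their true activity levels differ. More days per patient only reduce the day-to-day noise in each patient's own mean, and the primary outcome has already averaged over those days. The reason the article gives for the extra power, the count of patient-days, is thus not a reason for this comparison.

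What is at stake is how the two planned analyses of the primary outcome are read side by side. Someone who accepts the sentence would expect the multilevel analysis to be far sharper than the t test and would take a much smaller p value from it at face value. A gain of that size from the number of days alone would appear only if the days were treated as independent.

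**Working it through.** **Inputs.** From the Sample Size Calculation: difference 2000 steps, within-group SD 3000, 50 per group. From Statistical Analysis: alpha .05, with sidedness not stated. I take it as two-sided; a one-sided test would give 95.2%, so two-sided is the reading that fits 90%. The day-to-day SD, the loss rates and the missing-day patterns below are assumptions, because the article gives none.

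**1. The plan's own figure.** d = 2000/3000 = 0.667. The SE of the difference is 3000 × √(1/50 + 1/50) = 600 steps, and the noncentrality is 2000/600 = 3.33. Power from the noncentral t with 98 degrees of freedom is 91.0% (normal approximation 91.5%). The t test needs 49 per group for 90%. The stated 90% with 100 patients is reproduced.

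**2. Multilevel model, complete days.** Let steps on day j for patient i be a group mean plus a patient effect (variance τ²) plus day noise (variance σ²). The mean over 21 days has variance τ² + σ²/21. With 21 days for everyone, the generalised least squares estimate of the group effect is the difference between the group averages of the patient means, and

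SE = √[2(τ² + σ²/21)/50].

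The quantity in round brackets is the variance of the patient means, assumed to be 3000² = 9,000,000. So SE = √(2 × 9,000,000/50) = √360,000 = 600, whatever the split between τ² and σ². Day SDs of 1000, 2000, 3000 and 4000 all give 600.

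In 500 simulated trials (day SD 2000, complete days), power was 93.4% for the multilevel model and 93.2% for the t test, a net difference of one trial in 500. The mean multilevel SE was 597. Both figures carry a simulation error of about √(0.91 × 0.09/500) = 1.3 percentage points. The informative result is that they agree with each other.

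**3. Incomplete days.** SE and power by closed form, with missingness unrelated to steps:

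| Assumed pattern | Day SD | t test on means | Multilevel |
|---|---|---|---|
| 20% of days missing | 2000 | 601.7; 90.8% | 601.7; 90.8% |
| 20% of days missing | 4000 | 606.7; 90.4% | 606.7; 90.4% |
| 3 to 21 days per patient | 2000 | 608.6; 90.2% | 608.3; 90.2% |
| 3 to 21 days per patient | 4000 | 633.6; 87.8% | 629.9; 88.2% |

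The largest gain is 0.4 percentage points.

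**4. If 3000 were the SD of single days.** The averages would then vary less: SD 2854 at an assumed intraclass correlation of 0.9, and 1732 at 0.3. Power of the t test on the averages rises to 93.4% and above 99% respectively. The averaging delivers that gain, so the multilevel model still has no advantage.

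**5. Where a large gain would come from.** Treating 2100 patient-days as independent gives SE = √[2(τ² + σ²)/1050]. With σ = 2000, τ² = 9,000,000 − 4,000,000/21 = 8,809,524, so SE = √(2 × 12,809,524/1050) = 156. Over day SDs of 1000 to 4000 the range is 138 to 215, against the valid 600. A model grouped by patient, as planned, does not do this.

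**6. Power by number analysed** (t test, d = 0.667): 100, 91.0%; 97, 90.1%; 96, 89.8%; 90, 87.9%; 80, 83.8%.

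**The case against.** The sentence is an aside. The trial is sized on the t test, and neither the sample size, the alpha nor the first-listed analysis depends on it. The planned model is grouped by patient, so the clustering is not ignored. Exact equality needs complete days and no covariates, and a multilevel model can gain from covariates or from weighting patients by their number of recorded days. All of this is fair and keeps the point small. It does not rescue the sentence, because the reason it gives is the number of observations. The weighting gain is negligible in the cases tried, and patient-level covariates would help a regression on the averages as well. A difference between groups in trend over time would be another hypothesis, whereas the models are said to test the same ones.

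A reader might go further and infer that the 90% is itself wrong because it leaves no room for losses. The Introduction does cite an internet and mobile trial after rehabilitation, "but the high attrition rate in the randomized controlled trial (RCT) prevented the authors from drawing clear conclusions", and the Abstract plans to recruit the same 100 that the calculation requires. The document does not support that inference. The 90% is stated for 100 participants and is right for 100. An allowance may sit in the full protocol or in the appendix to which the simulation is referred, neither of which is shown. The cited trial concerned maintenance after rehabilitation; here the outcome spans 3 weeks and comes from a passive logger, and the feasibility study reports wear on 54 of 56 days (96%), though in only 8 patients over 1 week.

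A reader might also infer that the sponsor counts on the multilevel model as a reserve against dropout or a larger SD. No section says so.

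**Conclusion.** One statement is wrong as written: the multilevel models do not have much higher power for the group difference. With complete days their SE (600 steps) and power (about 91%) are those of the t test. With unequal days the gain was at most 0.4 percentage points under the assumptions tried. This rests on a random-intercept model with a constant group effect, no covariates and days missing independently of steps. The equality with complete days does not depend on the day-to-day SD, nor on whether 3000 is read as the SD of patient means or of single days.

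The stated power and sample size stand. That power falls to about 88% with 90 analysed and 84% with 80 is useful context under assumed losses, not an error in the article. The point is a correction to the power section that changes no design feature.

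**What to change.** In the Sample Size Calculation, delete the claim of much higher power together with its reason. Replace it with a statement that, for the group effect, the day-level multilevel model has essentially the same power as the t test on 3-week averages, and that any gain would come from covariates or from the handling of missing days, not from the count of patient-days.

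Add that the 90% refers to patients with an analysable 3-week average: 91% with 100 analysed and, if losses of 10% or 20% are assumed for illustration, about 88% and 84%.

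The cost is a few sentences. Sample size, tests and alpha are unchanged.
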